## Abstract

**Background:**

Arterial hypertension is highly prevalent but poorly controlled. Blood pressure (BP) reduction substantially reduces cardiovascular morbidity and mortality. Recent randomized, double-blind clinical trials demonstrated that azilsartan medoxomil (AZM) is more effective in reducing BP than the ubiquitary ACE inhibitor ramipril. Therefore, we aimed to test whether these can be verified under clinical practice conditions.

**Methods/Design:**

The “*Treatment with Azilsartan Compared to ACE-Inhibitors in Anti-Hypertensive Therapy*” (EARLY) registry is a prospective, observational, national, multicenter registry with a follow-up of up to 12 months. It will include up to 5000 patients on AZM or ACE-inhibitor monotherapy in a ratio of 7 to 3. A subgroup of patients will undergo 24-hour BP monitoring. EARLY has two co-primary objectives: 1) Description of the safety profile of azilsartan and 2) achievement of BP targets based on recent national and international guidelines for patients treated with azilsartan in comparison to those treated with ACE-inhibitors. The most important secondary endpoints are the determination of persistence with treatment and the documentation of cardiovascular and renal events. Recruitment commenced in January 2012 and will be completed by February 2013.

**Conclusions:**

The data obtained will supplement previous results from randomized controlled trials to document the potential value of utilizing azilsartan medoxomil in comparison to ACE-inhibitor treatment for target BP achievement in clinical practice.

## Background

Arterial hypertension is a highly prevalent disease, substantially impacting cardiovascular prognosis
[1]. Despite the availability of many safe and effective antihypertensive drugs, of which angiotensin converting enzyme (ACE) inhibitors are the most widely used, blood pressure (BP) is controlled in only 20% of hypertensive patients
[2]. An additional reduction of mean systolic BP in the order of 2 mmHg would result in a reduction of the rates of fatal stroke by 10% and of fatal myocardial infarction by 7%
[1]. There is clearly a need for drugs that are potentially more effective and safe while having a high tolerability and persistence rates.

Azilsartan medoxomil (AZM, TAK-491) is a recently developed angiotensin receptor blocker (ARB) that has a number of specific characteristics
[3]. It is structurally similar to candesartan except that it bears a 5-oxo-1,2,4-oxadiazolemoiety in place of the tetrazole ring
[4]. Further it has a carboxyl group at the 7-position of the benzimidazole ring, which is believed to result in insurmountable receptor antagonism
[3,5]. This insurmountable binding of AZM to the AT_1_ receptor may contribute to its potent and long-lasting antihypertensive activity.

### Azilsartan - clinical efficacy, safety and tolerability

Four studies compared the clinical efficacy of AZM with other ARBs. The studies included patients with primary hypertension and used ambulatory BP monitoring (ABPM) to determine BP lowering efficacy. AZM at a dose of 80 mg once daily provided superior BP lowering compared to the highest approved doses of olmesartan (40 mg), valsartan (320 mg) and candesartan (32 mg)
[6-9] (Table 
1).

**Table 1 T1:** Clinical trials conducted with Azilsartan to date (Phase III)

	**Duration**	**Patients**	**Intervention**	**Primary endpoint**	**Outcome**
Sica et al. 2011 [7]	24	984 patients	AZM 40 mg/d (n=327)	Change in 24-hour	AZM 40 mg/d: -14.9 mmHg
		Mean age: 58 years	AZM 80 mg/d (n=329)	mean SBP from baseline to week 24	AZM 80 mg/d: -15.3 mmHg
		Female: 48%	Val 320 mg/d (n=328)		Val 320 mg/d: -11,3 mmHg
		BMI: 31 kg/m^2^			(p<0.001)
		Race: 77% Caucasian			
White et al. 2011 [6]	6	1291 patients	AZM 40 mg/d (n=280)	Change in 24-hour mean SBP from baseline to week 24	AZM 40 mg/d: -13.4 mmHg
		Mean age: 56 years	AZM 80 mg/d (n=285)		AZM 80 mg/d: -14.5 mmHg (p=0.009 vs. OLM, p<0.001 vs. VAL)
		Female: 46%	Valsartan 320 mg/d (n=282)		
		BMI: 31 kg/m^2^	Olmesartan 40 mg/d (n=290)		Valsartan 320 mg/d: -10.2 mmHg
		Race: 65% Caucasian	Placebo (n=154)		Olmesartan 40 mg/d: -12.0 mmHg
					Placebo: -0.3 mmHg
Bakris et al. 2011 [8]	6	1275 patients	AZM 20 mg/d (n=283)		AZM 20 mg/d: -12.2 mmHg
		Mean age: 50 years	AZM 40 mg/d (n=283)		AZM 40 mg/d: -13.5 mmHg
		Female: 50%	AZM 80 mg/d (n=285)		AZM 80 mg/d: -14.6 mmHg
		BMI: 30 kg/m^2^	OLM 40 mg/d (n=282)		(p=0.038 vs. OLM))
		Race: 73% Caucasian	Placebo (n=142)	Change in 24-hour mean SBP from baseline to week 6	OLM 40 mg/d:-12.6 mmHg Placebo: -1.4 mmHg
Rakugi et al. 2012 [9]	16	622 patients	Azilsartan up to 40 mg/d (n=313)	Change in sitting trough clinic DBP from baseline to week 16 (LOCF)	Azilsartan: -12.9 mmHg
		Mean age: 57 years	Candesartan up to 12 mg/d (n=309)		Candesartan: -9.7 mmHg
		Female: 39%			(p=0.0003)
		BMI: 25.5 kg/m^2^			(SBP reduction at week 16: AZM –
		Race: 100% Japanese			21.6 mmHg, CAN −17.3 mmHg)
Bönner et al. 2013 [11]	24	884 patients	AZM 40 mg/d (n=295)	Change in sitting trough clinic SBP from baseline to week 24	AZM 40 mg: -10,2 mmHg
		Mean age: 57 years	AZM 80 mg/d (n=294)		AZM 80 mg: -10,5 mmHg
		Female: 48%	Rami 10 mg/d (n=295)		Rami 10 mg: -4,9 mmHg
		BMI: 30 kg/m^2^			(clinic SBPp<0.001)
		Race: >99% Caucasian			

*Legend*: *LOCF*, Loss of Continous Follow-up; *SBP*, Systolic Blood Pressure; *BMI*, Body Mass Index; *CAN*, Candesartan.

Treatment was generally well-tolerated with a similar rate of adverse events between AZM and placebo and low rates of 2% to 3% for the withdrawal due to adverse events
[10]. The most frequent adverse event was diarrhea in up to 2% of patients receiving the 80-mg dose compared with 0.5% of patients receiving placebo
[10]. Other adverse events included nausea, asthenia, fatigue, muscle spasm, dizziness and cough. A small and reversible increase in serum creatinine was observed in patients receiving AZM 80 mg. Low hemoglobin, hematocrit, and red blood cell counts were observed only in 0.2%, 0.4%, and 0.3% of patients receiving AZM, respectively.

Recently, a randomized trial compared the antihypertensive efficacy and safety of AZM to ramipril
[11]. This comparison is particularly important since ramipril is considered a benchmark antihypertensive drug that has not only been shown to be effective in lowering BP
[12] but also to reduce cardiovascular morbidity and mortality in patients at high risk in the landmark Heart Outcomes Prevention Evaluation (HOPE) trial
[13]. Patients in this comparative trial were assigned to receive daily doses of 40 mg AZM, 80 mg AZM or 10 mg ramipril. The primary efficacy endpoint was the change in clinic and ambulatory systolic BP from baseline. AZM 40 and 80 mg reduced both clinic and mean 24-hour systolic BP significantly more than ramipril at a dose of 10 mg did (clinic SBP −20.6 ± 0.9 with 40 mg and −21.2 ± 0.9 with 80 mg AZM vs. -12.2 ± 0.9 with ramipril) (Figure 
1). Adverse events leading to discontinuation of treatment were less frequent with both doses of AZM (2.4% and 3.1%) compared with ramipril (4.8%).

**Figure 1 F1:**
[figure not shown]
**Office blood pressure reduction in a comparative trial of Azilsartan Medoxomil (AZM) and ramipril (RAM)**[11]**.**

### Aim of the registry

Based on these data, a considerable improvement of BP control might be expected from using AZM in clinical practice. The prospective observational registry (EARLY) aims at documenting BP control and its impact on cardiovascular and renal events during 12 months of follow-up in patients with either AZM or ACE-inhibitor treatment.

## Methods/Design

The “*Treatment with Azilsartan Compared to ACE-Inhibitors in Anti-Hypertensive Therapy*” (EARLY) registry is a prospective, observational, national, multicenter registry with a follow-up of 12 months. The registry will enroll up to 5000 patients with arterial hypertension starting treatment on either AZM or any ACE inhibitor monotherapy in up to 1000 sites in Germany in a ratio of 7 (AZM) to 3 (ACE-inhibitors) (Figure 
2). While BP is regularly determined using office BP measurement, there is a subgroup of patients with ABPM using the Mobil-O-Graph® device. Data are recorded at baseline and will be prospectively documented during follow-up visits at 6 and 12 months or at the predefined end of the registry in December 2013 (Figure 
3).

**Figure 2 F2:**
[figure not shown]
**Principal design of EARLY.** Patients will be recruited on a consecutive basis, given their compliance with the in- and exclusion criteria defined, in a ratio of 7 (AZM) to 3 (ACE inhibitors).

**Figure 3 F3:**
[figure not shown]
Patient recruitment and follow-up.

The registry is conducted in accordance with the ethical principles that have their origin in the Declaration of Helsinki and adheres to the principles of Good Epidemiology Practice (GEP), and applicable regulatory requirements. The protocol was approved by the independent ethics committee in Freiburg and the ethics committee of the State Medical Council of Rheinland-Pfalz, Germany. EARLY has further been registered with the database of the Verband forschender Arzneimittelhersteller (VFA). Patients being enrolled into this registry have to provide written informed consent.

### Objectives

EARLY has two **co-primary objectives:** 1) Description of the safety profile of AZM. 2) Achievement of BP targets based on recent national and international guidelines for patients treated with AZM in comparison to those treated with ACE-inhibitors.

**Secondary objectives** are as follows: 1) Absolute and relative BP reduction with antihypertensive treatment over the duration of one year. 2) Documentation of the adherence to guidelines for the diagnosis and treatment of hypertension in ambulatory care. 3) Persistence understood as the mean duration of monotherapy and / or AZM based combination therapy during follow-up. 4) Documentation of adverse events. 5) Prospective documentation of cardiovascular and renal events. 6) A pharmaco-economic evaluation of AZM use.

Additional objectives in a subgroup of patients with ABPM are to document BP lowering and pulse pressure reduction over the 1 year follow-up considering prior and concomitant antihypertensive pharmacotherapy as well as BP at baseline, and BP control with AZM in comparison to ACE-inhibitors (specific ACE inhibitors will be considered given their sample size is sufficient). Second, BP values obtained from ABPM will be compared to corresponding office BP values. Finally, central systolic and diastolic blood pressure, cardiac output (per minute), peripheral resistance, augmentation index, and pulse wave velocity will be determined and compared between patients receiving AZM or ACE-inhibitor treatment.

### Selection of sites

The registry is performed in primary care offices in Germany, with a planned participation of up to 1000 sites. Centers will be selected from a database maintained at the Institut für Herzinfarktforschung, Ludwigshafen, in order to be representative for the ambulatory treatment of hypertension in Germany. The recruitment per physician is limited to a maximum of 30 patients.

### Selection of patients

Adult patients (≥ 18 years) with essential arterial hypertension are included on a consecutive basis, given they have provide written informed consent and fulfill the following two criteria: 1) Participants have either no anti-hypertensive treatment prior to inclusion or a prior non-RAS based antihypertensive monotherapy. 2) A monotherapy using AZM or any ACE-inhibitor is initiated at baseline.

Patients are excluded from participation if they 1) receive antihypertensive drugs for an indication other than hypertension (e.g. beta blockers or diuretics for heart failure), 2) have a history of alcohol, drug abuse or illegal drug addiction, 3) have a life expectancy of less than one year, 4) are pregnant or breast feeding, or 5) are participating in other trials or registries. Further to this, patients with contraindications as to the summary of product characteristics of AZM or the ACE inhibitors will not be permitted. Patient recruitment started in January 2012 and will end on February 28^th^ 2013 at the latest or as soon as the recruitment target of 5000 patients is met.

### Documented variables

Table 
2 displays the variables documented at baseline and at the follow-up visits at 6 and 12 months. These include socio-demographic variables, BP / heart rate, anamnestic concomitant disease, risk factors, anti-hypertensive treatment including dose, further pharmacotherapy, investigations, laboratory values, incident concomitant disease, lethal and non-lethal event rates and adverse events. In the subgroup of patients with ABPM respective parameters will be documented.

**Table 2 T2:** Variables documented at baseline, and at 6 and 12 months of follow-up

	**Baseline**	**6 months FU**	**12 months FU**
Socio-demographic variables ^1^	X	X^9^	X^9^
Blood pressure / heart rate	X	X	X
Anamnestic concomitant disease ^2^	X		
Risk factors ^3^	X		
Anti-hypertensive treatment incl. dose	X	X	X
Further pharmacotherapy ^4^	X	X	X
Further investigations ^5^	X		
Laboratory values ^6^	X	X	X
ABPM ^7^ (subgroup)	X	X	X
Event rate (lethal / non-lethal)		X	X
Incident concomitant disease ^8^		X	X
Adverse events		X	X

Legend:

1) age, gender, height, weight, body mass index (computed).

2) heart failure (including NYHA class), coronary artery disease, stroke / transitory ischemic attack, atrial fibrillation, peripheral arterial disease, diabetes mellitus (including duration), kidney disease (including glomerular filtration rate <60 ml/1.73m^2^, dialysis or transplantation), malignancy, chronic obstructive pulmonary disease, depression and other severe diseases.

3) hypercholesterolemia, hyperlipidemia, smoking (present, past or never, including duration).

4) other than antihypertensive drugs: nitrates, platelet aggregation inhibitors, oral anticoagulants, statins or antidepressive drugs.

5) signs of left ventricular hypertrophy (ECG or Echo), intima / media thickness > 0.9 mm or plaque, ankle-brachial index (ABI) < 0.9, pulse wave velocity > 12 ms, microalbuminuria.

6) hemoglobin, glucose, bA1c, creatinine, sodium, potassium, calcium, phosphate, total cholesterol, LDL-C, HDL-C, triglycerides, C-reactive protein, uric acid, urinary albumin concentration and albumin to creatinine ratio (all if available within three months prior to visit.

7) mean blood pressure and heart rate during daytime, nighttime and 24-hour average.

8) corresponding to 2) including whether patients were hospitalized and for how long.

9) weight only.

### Quality assurance

There are three strategies for data quality checks: validations that occur at the time of data entry (i.e., “front-end”), a second, more sophisticated quality control program that runs as a prelude to the creation of the analysis data set and on-site data monitoring. Front-end data checks are advantageous because mistakes are caught and corrected at the time of entry – a system that is efficient for data collectors. Certain data elements can be required, while other variables may allow for missing values. Additionally, parameters will be defined to allow entry of only those records that meet inclusion criteria. Prior to the creation of the analytic dataset, more extensive quality control processes are performed. These checks, programmed in SAS, include parent–child edits, consistency edits, and data transformations that will facilitate analyses. Source documentation and data accuracy will be verified by site visits in randomly selected 5% of the sites.

### Data management and statistics

Data entry is performed by the physician or study nurse via a secure website directly into an electronic database. This approach allows online checks for plausibility and integrity.

The sample size for this registry was determined aiming to provide a sufficient precision of the primary endpoint, e.g. BP target achievement of <140/90 mmHg with a monotherapy of AZM or an ACE-inhibitor. Based on the aforementioned trial published by Bönner et al.
[11] comparing AZM with the ACE-inhibitor ramipril, target achievement rates of 50-60% can be expected with AZM monotherapy versus 30-40% with ramipril. Because of the two principal research objectives each confidence interval (CI) is determined using the Bonferroni method for the adjusted confidence probability (1–0.05/2). For the AZM group a precision of the determined control rate of ±2.1% is planned (width of the 97.5% CI 4.2%), while a ±3.2% precision is deemed sufficient for the ACE-inhibitor arm. For this purpose 2849 patients have to be recruited for the AZM arm and 1178 patients for the ACE-inhibitor arm. Considering a design effect of 1.15 (because of the cluster-sampling design and allowing a drop-out of 5%), 3500 patients have to be recruited for the AZM and 1500 patients for the ACE-inhibitor arm, resulting in a total population of 5000 patients. There will be a proportional recruitment of patients until February 28^th^ 2013. In case the recruitment target of 5000 patients is not met, a reduced precision of the primary objective will be accepted.

All variables collected in the eCRF as well as the data obtained from the quality of life assessments and all derived parameters will be used in the statistical analysis. Binary, categorical, and ordinal parameters will be summarized by means of absolute and percentage numbers within the various categories (including ,,missing data‟ as valid category at baseline). Numerical data will be summarized by means of standard statistics (i.e. number of available data, number of missing data, mean, standard deviation, minimum, median, maximum, lower and upper quartile). In addition, adequate graphs (e.g. bar charts, box-whisker plots) may be presented to summarize the results for some parameters. Time-to-event variables will be analyzed via a Cox proportional hazard regression model presenting hazard ratios and the corresponding 95% confidence intervals (CI). In addition Kaplan-Meier curves will be presented for these variables. Two-sided 95%-CI will be presented for important parameters, but should be interpreted in an exploratory descriptive way. Further multivariable analyses will be performed according to the statistical analysis plan (SAP). Formal statistical tests will not be performed within the statistical analysis. A report including descriptive statistics of all documented parameters will be generated for the overall patient population. Depending on the variable(s) of interest, additional selection criteria for patients (e.g. subgroup analyses) considered in specific analyses may be used, if considered useful during the statistical analysis. Details on the selection criteria used will be given in the SAP and in the statistical section of the report. The statistical analysis will be performed using SAS (release 9.2 or higher; Cary, NC, USA).

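### The registry is sized on 97.5% intervals for blood-pressure control, but the analysis text promises 95% intervals without exempting the co-primary endpoint

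*Protocol article*

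**What the plan says.** Both statements stand in the Protocol article, section Data management and statistics, in adjacent paragraphs.

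The sample-size paragraph refers to the two principal research objectives and says that "each confidence interval (CI) is determined using the Bonferroni method for the adjusted confidence probability (1–0.05/2", which is 97.5%. For azilsartan, "a precision of the determined control rate of ±2.1% is planned (width of the 97.5% CI 4.2" percentage points; for the comparator, "while a ±3.2% precision is deemed sufficient for the ACE-inhibitor arm". The expected rates are given as "target achievement rates of 50-60% can be expected with AZM monotherapy versus 30-40% with ramipril". From these it concludes that "2849 patients have to be recruited for the AZM arm and 1178 patients for the ACE-inhibitor arm". The inflation to 3500 and 1500 is introduced by "Considering a design effect of 1.15 (because of the cluster-sampling design and allowing a drop-out of 5" percent.

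The analysis paragraph then says: "Two-sided 95%-CI will be presented for important parameters, but should be interpreted in an exploratory descriptive way". It also gives 95% intervals for hazard ratios and excludes formal tests. The 97.5% level does not appear there. Further multivariable analyses and patient-selection criteria are left to the SAP; the confidence level is not.

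Under Objectives, the first co-primary objective is a description of the safety profile of azilsartan. The second is achievement of blood-pressure targets compared with ACE inhibitors. A precision target is given only for the control rates.

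**The concern.** The article fixes a confidence level twice, and the two levels differ. The control rate is the endpoint for which the registry was sized, so the natural reading counts it among the important parameters and gives it a 95% interval. The sample-size paragraph promises an interval at 97.5%.

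Two things are at stake. First, the stated precision and the 5000 patients are justified by a level that the analysis text does not use. Second, the multiplicity allowance made at the design stage is not carried into the results, so the published intervals would have a weaker joint guarantee than the one planned. A reader of the results could not tell which interval the registry was designed to deliver.

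**Working it through.** **Inputs, all from the sample-size paragraph.** Half-widths d of 0.021 (azilsartan) and 0.032 (ACE inhibitor); expected rates of 50–60% and 30–40%; design effect 1.15; drop-out 5%; final numbers 3500 and 1500. The article does not say which rate within each range was used. I took p = 0.50 and p = 0.40, the ends nearest one half, because they reproduce the stated numbers.

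**Step 1: reproduce the plan's figures.** For a single proportion, n = z² p(1 − p)/d². At 97.5%, z = 2.2414 and z² = 5.0239.
- Azilsartan: 5.0239 × 0.25 / 0.000441 = just over 2848, which rounds up to the stated 2849.
- ACE inhibitor: 5.0239 × 0.24 / 0.001024 = 1177.5, which rounds up to the stated 1178.

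With inflation by 1.15/0.95 these become 3449 and 1426. The stated 3500 and 1500 are somewhat higher, which fits rounding up to 5000 in a 7:3 split.

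**Step 2: the same calculation at 95%.** With z = 1.960, n is 2178 and 901. No rate in the stated ranges brings the 95% calculation up to 2849 or 1178: the largest values there are 2178 and 901. After inflation the total would be (2178 + 901) × 1.15/0.95 ≈ 3727.

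**Step 3: width of the reported intervals.** Evaluable patients are 3500 × 0.95 = 3325 and 1500 × 0.95 = 1425. The half-width is z × √(1.15 × p(1 − p)/n).

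| Arm | 97.5%, as planned | 95%, as the analysis text reads |
|---|---|---|
| Azilsartan, p = 0.50 | ±2.08 points | ±1.82 points |
| ACE inhibitor, p = 0.40 | ±3.12 points | ±2.73 points |

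At the other ends of the expected ranges the figures are ±2.04 against ±1.79 (azilsartan, p = 0.60) and ±2.92 against ±2.55 (ACE inhibitor, p = 0.30). The ratio is always 1.960/2.2414 = 0.874, or 12.6% narrower, whatever the rate, sample size or design effect.

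**Step 4: joint coverage.** By Bonferroni, two 95% intervals jointly cover with probability at least 1 − 2 × 0.05 = 90% (0.95² = 90.25% if independent). Two 97.5% intervals give at least 1 − 2 × 0.025 = 95%.

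**Step 5: precision if 95% is what is meant.** With 2849 and 1178 patients before inflation: 1.960 × √(0.25/2849) = ±1.84 points and 1.960 × √(0.24/1178) = ±2.80 points.

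**The case against.** The strongest reply is that nothing harmful follows. A correctly computed 95% interval is valid at 95%; the analysis paragraph calls the intervals exploratory, no test or decision rule depends on them, and 5000 patients give better precision at 95% than was promised. The phrase about important parameters is also general and does not expressly rule out 97.5% for the control rates. All of this is fair, and it limits the severity. It does not remove the contradiction: the level that justifies the sample size is not the level the analysis text announces, and the article does not say which governs the co-primary endpoint. An unseen SAP could settle the question only by departing from the ordinary reading of one of the two paragraphs.

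A reader might also infer that the intervals will ignore clustering by site. They would then be about 18.5% narrower than planned (±1.70 and ±2.54 points), and a nominal 95% interval would cover about 93.2% at a design effect of 1.15. The article does not support this. It names no variance method, neither requiring nor excluding a cluster adjustment, and a condensed article may leave that to the SAP.

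Nor can the design effect itself be shown to be wrong from the site rule that "The recruitment per physician is limited to a maximum of 30 patients". Thirty is a cap, no intra-site correlation is stated, and the precision is per arm. At 5000/1000 = 5 patients per site and a 7:3 split, the average cluster is 3.5 azilsartan and 1.5 ACE-inhibitor patients, so a correlation worked out from 5 per site would not apply to either arm.

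**Conclusion.** The point stands as an internal inconsistency of moderate weight. The sample-size arithmetic is right, but it belongs to 97.5% intervals, and the analysis text offers 95% intervals with no exception for the co-primary control rates. The documented effect is that intervals come out 12.6% narrower than planned, with a guaranteed joint coverage of 90% in place of 95%, and that the stated patient numbers do not follow from the stated analysis.

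The half-widths in points assume full recruitment, 5% drop-out, a design effect of 1.15 and rates of 50% and 40%; the 12.6% needs none of these. The 95% intervals are too narrow only against the plan's own 97.5% standard. The point estimates, the description of safety and the adequacy of 5000 patients are not called into question.

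**What to change.** Choose one level for the co-primary control rates and use it in both paragraphs.

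- **Keep the sizing.** Add to the analysis paragraph that the co-primary control rates are reported with 97.5% intervals and all other parameters with 95% intervals. The cost is primary intervals about 14% wider than at 95% (2.2414/1.960 = 1.144).
- **Or keep 95%.** The first co-primary objective is a description of safety without a precision target, so the Bonferroni step can be dropped from the sample-size paragraph. The precision of 2849 and 1178 patients is then restated as about ±1.8 and ±2.8 points at 95%. The cost is giving up the 95% joint guarantee.

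In either case, confirm that the control-rate intervals use a site-clustered variance, consistent with the design effect of 1.15 already assumed. This asks for confirmation only, since the text does not exclude it. The work is a sentence or two of wording and, if not already in place, one option in the analysis code.
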